## Abstract

**Background:**

Exposure to patient or user suicide (PUS) is identified as a challenging occupational hazard for mental health and social work professionals. Professionals exposed to PUS may encounter several ranges of emotional, traumatic or professional impacts in the aftermath. A high proportion of exposed professionals reports a lack of support in the aftermath of PUS. SUPPORT is a postvention program designed to provide a comprehensive, adaptative and effective support to professionals impacted by PUS. The aims of the SUPPORT-S study are to (1) improve the design of the SUPPORT program, (2) evaluate the effectiveness of the program to buffer the emotional, traumatic and professional impacts and to improve the perceived social support for professionals exposed to PUS, and (3) provide more insights into the consequences of PUS on both professionals and organizations.

**Method:**

The SUPPORT-S study is a mixed method collaborative and participatory action research. The simultaneous and complementary collection and analysis of qualitative and quantitative data will offer an in-depth evaluation of the implementation and the effectiveness of the program. The qualitative evaluation includes: (a) an ethnographic observation; (b) 25 semi-directed interviews with randomized participants; (c) an activity analysis with providers of the program; and (d) collaborative sharing of the results with providers and participants. The quantitative evaluation includes pre- and post-measures in participants of: (a) emotional impact (*Differential Emotions Scale IV*); (b) traumatic impact (*Impact of Event Scale-Revised*); (c) professional impact (non-validated questionnaire); and (d) perceived social support (*Perceived Social Support Scale for Professionals*). The action research design will rely on: (a) the cycling process of implementation/evaluation/data sharing/adjustment and (b) the participatory approach through data sharing with providers and participants. Triangulation, saturation, randomization, and participatory design will also reduce the risk of biases and will improve the generalizability of conclusions.

**Expected Results:**

We expect the SUPPORT-S study to evaluate and improve the design of the SUPPORT program to effectively help professionals to cope with PUS.

**Conclusion:**

The results of the study will allow us to disseminate an effective and adaptive postvention program for professionals and institutions encountering PUS.

## IntroductIon

Exposure to patient or user suicide (PUS) has been identified as a frequent and challenging occupational hazard for mental health and social work professionals (Gulfi et al., 2010; Séguin et al., 2014; Castelli Dransart et al., 2017; Leaune et al., 2019a). For instance, between 51 and 82% of psychiatrists (Castelli Dransart et al., 2017), 46.9% of psychiatric trainees (Leaune et al., 2019a), between 22 and 39% of psychologists (Castelli Dransart et al., 2017), 55% of nurses (Takahashi et al., 2011) and 33% of social workers (Jacobson et al., 2004) will experience PUS during their training or career. Cerel et al. (2014) identified a “continuum of survivorship” after suicide, distinguishing those who are exposed to, affected by, or bereaved long-term or short-term by suicide. Considering PUS, all the members of the staff may encounter high levels of psychological distress and professional difficulties in the aftermath, including emotional, traumatic, and professional impacts (Séguin et al., 2014; Castelli Dransart et al., 2017; Leaune et al., 2019a, b). The emotional impact frequently includes shock, guilt, sadness, anger, failure, shame, and anxiety. Stress and traumatic reactions are also reported, including acute stress and posttraumatic stress disorders. Regarding professional impact, PUS may challenge the feelings of self-confidence and professional competence. A fear and avoidance of suicidal individuals, an impairment in professional decision-making or a decrease in work performance are notably reported. Some of the exposed professionals may also experience grief reactions or disenfranchised grief, i.e., a grief that is denied the right to exist because the impact of the loss is not recognized by peers, superiors or society (Doka, 1989). The majority of professionals will positively manage the impact of PUS through professional growth and encounter it as a learning and beneficial experience. In contrast, a minority of professionals will show high levels of impacts, with negative personal and professional outcomes. The term “second victims,” proposed to designate professionals exposed to adverse medical events in patients, has thus been used in the case of professionals impacted by PUS (Scott, 2019). The negative impact of PUS is significantly associated with a closeness to the deceased, a high level of the professional–client relationship and a lack of support and training. Castelli Dransart et al. (2015) notably reported that the lack of support in the aftermath was a risk factor for higher traumatic impact in the aftermath of PUS.

Postvention refers to the activities developed in the aftermath of a suicide to prevent negative health outcomes and facilitate recovery among the bereaved (Andriessen, 2009). Despite the growing evidence on the impact of PUS, the lack of institutional support in the aftermath has been widely documented (Ruskin et al., 2004; Castelli Dransart et al., 2015; Leaune et al., 2019a, b). Moreover, the literature on postvention programs dedicated to the support of health and social work professionals remains scarce. In retrospective studies, however, the participants have reported that support from peers, superiors or their institution can be both a protective factor and a predictor for adaptative coping strategies and lower levels of emotional, traumatic, and professional impacts (Castelli Dransart et al., 2015, 2017). Only one study qualitatively explored the effects of a half-day retreat dedicated to health and social work professionals previously exposed to PUS (Figueroa and Dalack, 2013). All respondents reported that participating in the retreat was a beneficial and helpful experience, highlighting the positive effects of the group intervention design. The effectiveness of this program to reduce the emotional, traumatic or professional impact of PUS was not assessed.

Hence, research dedicated to the development and evaluation of comprehensive and adaptive programs providing support to mental health professionals and social workers exposed to PUS is needed. In line with this urgent need for social change, this article aims to describe (1) the design and implementation of a postvention program (SUPPORT) for professionals exposed to PUS and (2) the protocol of the SUPPORT-S research-action study evaluating and improving the design of the SUPPORT program to effectively help professionals to cope with PUS.

## Method

### Development of the SUPPORT Program

The Center for Suicide Prevention (CSP) is an ambulatory care unit located in Lyon, France, that provides several types of suicide prevention activities, including brief contact interventions for people showing suicidal ideation or those who attempted suicide, outreach interventions for people showing suicidal behaviors, postvention counseling for individuals or family bereaved by suicide and information and training on suicide prevention.

According to the model of support for professionals after adverse events developed by Scott et al. (2010) our pluri-professional team of the CSP (psychiatrists, social and work psychologists, nurses, and psychiatric residents) designed a four-stage postvention program for mental health and social work teams exposed to PUS (SUPPORT, see Figure 1). The Scott three-tiered integrated model (STTIM) of interventional support after adverse event was developed by Scott et al. (2010) to provide an on-demand rapid intervention, ranging from immediate first aid support through peers and superior support to professional counseling for second victims. The STTIM relies on both local support from peers and superiors and supportive interventions by a trained team dedicated to the impact of adverse events on professionals.

**FIGURE 1 F1:**
[figure not shown]
Schematic overview of the SUPPORT program.

Inspired and adapted from the STTIM, SUPPORT is a 6-week program divided into four distinct stages. The three following stages are mandatory: (a) basic emotional first aid at the local level; (b) team-based 1- to 2-h supportive intervention in the institution; and (c) follow-up, late detection. A fourth optional stage including long-term support and training or workshops on suicide prevention may be provided to professionals. The objectives of the SUPPORT program are to (1) buffer the traumatic, emotional and professional impacts in professionals, (2) improve the support perceived by exposed professionals, and 3) promote the return to normal functioning in the institution exposed to PUS.

#### Stage 1: Emotional First Aid

The first stage of the program includes early contacts by the CSP with the head of the exposed team (head of department, physicians, chief nurse, etc.) to provide them with an organizational framework of structured and synchronized crisis management. According to the guidelines for postvention interventions (Andriessen et al., 2019), the objective of this first stage is to build a crisis team dedicated to the management of the aftermath of PUS and the deployment of basic emotional first aid for the exposed professionals. The detection and initial support of highly impacted professionals (acute stress disorder, depressive reaction, suicidal ideation, etc.), the prevention of suicide contagion and the orientation to mental health care for those who are highly impacted are the most crucial issues of this first stage of the SUPPORT program. Individual consultations are notably proposed to the most strongly impacted professionals through a fast-track referral to the CSP. Stage 1 thus aims to promote basic emotional first aid and early detection for those who were the most impacted through local support from peers and superiors during the first days following a PUS, through the building of a crisis team.

#### Stage 2: Team-Based Intervention

The team-based intervention consists of a 1- to 2-h intervention in the institution where the suicide occurred, driven by two professionals (e.g., a psychiatrist or psychologist and a nurse) from the CSP in the month following a PUS. All of the exposed professionals are invited to participate in the intervention, during which a debriefing of the event and its impacts is performed. Exposed professionals are offered a supportive space to freely express their feelings about, emotions toward and experience of PUS. The intervention on the entire team aims to buffer the emotional, traumatic, and professional impacts, both in individuals and in the working team. In particular, the presence of the professionals who discovered the corpse or performed resuscitation techniques, those who were the closest of the deceased and those who were the most impacted is encouraged. Stage 2 thus aims to provide professional emotional aid at institutional level, through an in-depth team-based debriefing intervention.

#### Stage 3: Late Detection and Counseling

The third stage of the program seeks to perform late detection and counseling support for professionals who are strongly affected or traumatized by exposure to PUS. Those who feared attending the team-based intervention stage may notably receive individual debriefing during this stage. Stage 3 aims to promote the return to normal functioning in the institution, at both the individual and organizational levels. When stage 3 has not been effective in ensuring the recovery among professionals, a fourth stage can be added to properly support the impacted team.

#### Stage 4: Optional Long-Term Support

This optional stage is notably delivered if several suicides occurred or if the whole team is highly impacted by the suicide(s). The support of the management team and the close collaboration with the CSP are the most important components of this stage. A second debriefing intervention or a 3-hour suicide prevention training may be provided to the whole team. Workshops on the means and actions seeking to improve the prevention of suicidal behaviors or the support of professionals in the exposed setting are encouraged and organized, to involve impacted professionals in proactive and meaningful actions related to PUS. Stage 4 can last from one to three months and aims to provide in-depth long-term support for teams and institutions that have been strongly impacted by PUS.

### The SUPPORT-S Study

#### Study Objectives

##### Primary objective

The primary objective of the SUPPORT-S study is to improve the design of the SUPPORT program through the participatory involvement of professionals who deliver the intervention and those who receive it.

##### Secondary objectives

The SUPPORT-S study aims to evaluate the effectiveness of the SUPPORT program to buffer the emotional, traumatic and professional impacts and to improve the perceived social support for professionals exposed to PUS. The SUPPORT-S study also seeks to provide more insights into the consequence of PUS on both professionals and the organization and to identify markers that may help in implementing programs adapted to different professional settings.

#### Study Setting

The SUPPORT-S study will take place in Rhône, France, which is the geographical area of intervention for the CSP. The SUPPORT program is designed to be implemented in the following institutions: psychiatric hospitals, general hospitals, nursing homes and social work institutions. The study will start in February 2020 and last 18 months. Every psychiatric and general hospitals, nursing homes and social work institutions of the geographical area will receive in February 2020 detailed information on the SUPPORT-S study. A mail and an email will be sent to all executive managers.

#### Inclusion and Exclusion Criteria

Every professional working in the institution in which PUS occurred are eligible for participation in the SUPPORT-S study, without any exclusion criteria. Only professionals who do not agree to participate will not be included in the study but they will receive the postvention intervention if they wish to. The eligible professionals will be informed of the concepts, design and running of the study through an information sheet and oral explanations at inclusion.

#### Study Design

SUPPORT-S is a mixed method collaborative and participatory action research study, including a total of five SUPPORT interventions over a total of 15 months (Figure 2). SUPPORT-S seeks to evaluate both the effectiveness of the program from the perspective of professionals who receive the intervention (i.e., participants) and those who deliver it (i.e., providers) through an iterative participatory process.

**FIGURE 2 F2:**
[figure not shown]
Schematic overview of the SUPPORT-S study.

##### Action research

Action research is an approach that involves active collaboration *in situ* between researchers and participants to develop a process through knowledge building and social change (Lewin, 1946). Action research gives credence to the development of powers of reflective thought, discussion, decision, action, evaluation and revision by people or professionals participating in a collective research, through active participation during iterative sequences of those who have to carry out the work in the exploration of problems that they encounter (Adelman, 1993). The affective and cognitive involvement of participants is critical for the production of empirical knowledge and social modifications in professional practices. Cordeiro and Soares (2018) identified the following four principles of action research: (1) participation and collaboration; (2) a cycle of implementation, action, reflection and adjustment; (3) knowledge building that considers participants’ realities; and (4) social change and problem solving. These principles will be assumed in the SUPPORT-S study through the cycling process of local implementation/evaluation/reflection/adaptation and the active participation of professionals in the evaluation process through restitutions of the results and the conditions of the implementation. The action research process will be held through the following three main activities: (1) the collaborative sharing of results for all professionals after each SUPPORT intervention, (2) the cycling process for each SUPPORT intervention, and (3) the final collaborative sharing of results at the end of the study.

The *collaborative and participatory approach* will notably rely on the collaborative sharing of results, during which professionals (i.e., participants and providers) will be allowed to express their feelings about and experience with the SUPPORT program to propose adjustments for the program. The discussion, revision and validation of the results by the participants ensure their social relevance for the modification of practices in the institution and the implementation of new professional postures in professionals. This approach thus has a transformative role in the pluri-professional collective workforce rather than only focusing on individuals by involving them as active actors and not only participants of the research (Durif-Bruckert and Gonin, 2011; Budig et al., 2018). Moreover, the collaborative approach is based on the implications of social sciences researchers and clinical researchers who are also providers of the program. According to the notion of the “expanded scientific community” developed by Oddone et al. (1981), our participatory research action design thus involves a pluri-professional collaboration between participants, providers and researchers. This concept was developed to produce in-depth and empirically grounded knowledge on work-related psychosocial risk prevention and emphasizes the importance of the social context to improve efficacy and well-being in professionals. The lack of institutional support reported by professionals in the aftermath of PUS indicates the need to drive a substantial social change in institutional practices regarding postvention issues. The research action design of the study thus aims to allow the dissemination of a comprehensive and adaptative intervention among different institutions and professional settings. The collaborative and participatory approach of the SUPPORT-S study is understood at the same time as a way to gain effectiveness in the intervention, as a way to limit the biases related to mixed method design, and as an ethical posture in the research process and the interpretation of the results.

The *cycling process* of the SUPPORT-S study will be one of the key components of the action research design. Indeed, the local implementation of the SUPPORT program after a PUS will be performed throughout the following repeated process: (a) implementation, (b) qualitative and quantitative evaluation, (c) collaborative sharing of the results, and (d) adjustment of the program according to the restitution and evaluation (Table 1). Notably, the reflection on and modification of the SUPPORT program after each local implementation will ensure the cycling process of implementation/evaluation/reflection/adaptation through the active participation of both providers and participants. For each local implementation, the sequence will be repeated, and the program will be progressively modified, revised and adapted according to the cycling process. The revision and adaptation of the SUPPORT program after each implementation, through the active participation of providers and participants, will improve its effectiveness and relevance to help professionals in coping with PUS. Moreover, the cycling process is a methodological means to ensure the collaborative and participatory approach of the study, as providers and professionals are proactively involved in the research process.

**TABLE 1 T1:** The cycling process of the SUPPORT-S study.

Stage of the cycling process	Actions
Implementation	The CSP is informed of a PUS through emails or phone calls by the chief department of the institution where it occurred. Through a partnership developed with the Regional Health Agency, the CSP can be informed of every PUS occurring in nursing homes or social work organizations in the area and contact the chief department. After oral and written information of all exposed professionals in the institution, the SUPPORT program is implemented in the setting
Evaluation	• Collection of qualitative data: ethnographic observation, five individual semidirected interviews with participants, activity analysis with the SUPPORT program providers • Collection of quantitative data: traumatic impact (IES-R), emotional impact (DES-IV), professional impact (non-validated scale) and perceived support (P3SP) among participants/exposed professionals • Merging of the qualitative and quantitative data • Data analysis and report
Collaborative sharing of the results	Discussion, revision and validation of the results between researchers, providers and participants (workshop). Participants and providers freely express their feelings about and experience with the SUPPORT program to propose an adaptation of the program
Adaptation	Adaptation of the SUPPORT program (content, form) according to the revisions proposed during the collaborative sharing of data, before the next implementation

*CSP, Center for Suicide Prevention; PUS, Patient or user suicide; IES-R, Impact of Event Scale – Revised; DES-IV, Differential Emotions Scale – IV; P3SP, Perceived Social Support Scale adapted for Professionals.*

##### Mixed method evaluation

Mixed method studies have been shown to be effective in evaluating the implementation of new prevention programs in mental health (Palinkas et al., 2011). Mixed methods design focuses on collecting, analyzing and merging both quantitative and qualitative data into one study. According to the taxonomy of mixed method studies described by Palinkas et al. (2011), the structure of the SUPPORT-S study relies on a simultaneous collection of qualitative and quantitative data. Regarding the function, the two datasets will be collected in complementarity, e.g., qualitative data will be used to provide depth of understanding, and quantitative data will be used to provide breadth of understanding. The process of data analysis will be performed by merging the two datasets and actually bringing them together. The SUPPORT-S study is thus designed as a simultaneous complementary merging mixed method study.

#### Data Collection

According to the mixed method research design of the study, quantitative and qualitative data will be simultaneously and complementarily collected to obtain an in-depth evaluation of the implementation and effectiveness of the SUPPORT program (Figure 3).

**FIGURE 3 F3:**
[figure not shown]
Participants’ trajectories in the SUPPORT-S study.

##### Quantitative data

A collection of individual quantitative data will be performed before (T0) and after (T1) the SUPPORT program among professionals exposed to a PUS. Sociodemographic data and information on the therapeutic relationship with the deceased will be collected at T0. A pre/post measure of emotional, traumatic and professional impacts and perceived social support will be performed at T0 and T1.

The following sociodemographic characteristics of participants will be collected at T0: age, gender, profession, and years spent working in the organization.

The following information on the relationship between the professional and the event or the patient or user who died by suicide will be collected at T0: connection with the deceased, discovery of the corpse, resuscitation techniques used, being at work or not the day of the event, and therapeutic alliance with the deceased.

The traumatic impact will be assessed at T0 and T1 through the French version of the *Impact of Event Scale-Revised* (IES-R; Horowitz et al., 1979; Weiss and Marmar, 1997; Brunet et al., 2003). The IES-R is a 22-item self-report questionnaire assessing intrusion, avoidance and hyperarousal symptoms in the previous seven days before completion. Each item is rated on a 5-point Likert scale ranging from 0 (not at all) to 4 (extremely), for a total score of 88. According to previous literature, we will retain a cut-off score of 24/88 to indicate a significant traumatic reaction (Bienvenu et al., 2013) and a cut-off of 34/88 for PTSD (Asukai et al., 2002). The French version of the IES-R shows a good internal consistency (alpha coefficients ranging from 0.81 to 0.93) and satisfactory test-retest reliability (correlations coefficients ranging from 0.71 to 0.76) (Brunet et al., 2003).

The emotional impact will be obtained at T0 and T1 through the French version of the *Differential Emotions Scale IV* (DES-IV; Ricard-St-Aubin et al., 2010). The DES-IV is a 36-item questionnaire assessing the level of expression of the twelve following emotions: interest, joy, surprise, anger, contempt, disgust, sadness, fear, guilt, shame, shyness, and self-hostility. The emotions are measured through a 6-item Likert scale ranging from 1 (rarely or never) to 5 (very often), for a total score ranging from 36 to 180. The DES-IV shows good temporal stability (correlations coefficients ranging from 0.49 to 0.79) (Ricard-St-Aubin et al., 2010).

The professional impact will be assessed at T0 and T1 through a non-validated 18-item questionnaire built by our pluri-professional team and adapted from non-validated questionnaires on self-efficacy at work (self-confidence, problem-solving, and decision-making) and modifications in practice. The participants will be asked through close-ended questions about the self-perception of their effectiveness at work, the perception of modification in their professional practice and the type of modification that they perceive. Regarding the self-reported modifications in professional practice, a fear and avoidance of suicidal patients, an increased tendency to hospitalize patients, a fear of granting passes for patients and a prolonged duration of hospitalization are considered negative professional impacts. A better assessment of suicidal ideation in patients, an increased tendency to ask advice to colleagues, a better trackability of information in patients’ files and an interest in suicide prevention are considered positive professional impacts. Regarding self-efficacy, the perceived loss of self-confidence or self-control and perceived difficulties in problem solving or decision-making will be considered as negative professional impacts. The presence of at least three items indicating a negative impact on professional practice or self-efficacy will be considered as a negative professional impact.

Perceived support will be assessed through the *Perceived Social Support Scale for Professionals* (P3SP; Collange et al., 2016). The P3SP is a 12-item questionnaire evaluating the following four types of perceived social support provided by peers, superiors or the institution in the context of the workplace: (1) instrumental support (e.g., material support, technical assistance), (2) emotional support (e.g., being listened to), (3) informational support (e.g., advice, information, counseling), and (4) esteem support (e.g., positive feedback, constructive appreciation). The satisfaction regarding the four types of perceived support is assessed through a 4-item Likert scale ranging from 0 (not satisfied) to 3 (very satisfied), for a total score ranging from 0 to 36. The P3SP shows good sensitivity and specificity (Collange et al., 2016). Three scores are especially measured by the P3SP questionnaire: (1) level of perceived support from peers and collaborators (from 0 to 12), (2) level of perceived support from the institution (from 0 to 12), and (3) level of satisfaction of perceived support from superiors (from 0 to 12). The P3SP shows very good internal consistency (Cronbach’s alpha ranging from 0.82 to 0.93) (Collange et al., 2016).

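### T1 is tied to the end of a program whose length is stated inconsistently; if T1 follows the optional stage 4, teams chosen partly for slow recovery are measured later

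*Protocol article*

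**What the plan says.** **Timing of measurement.** Under Quantitative data: "A collection of individual quantitative data will be performed before (T0) and after (T1) the SUPPORT program among professionals exposed to a PUS". The text gives no calendar time, window or interval from the suicide.

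**Length of the program.** Under Development of the SUPPORT Program: "SUPPORT is a 6-week program divided into four distinct stages". The same paragraph makes the first three stages mandatory and describes the last this way: "A fourth optional stage including long-term support and training or workshops on suicide prevention may be provided to professionals". Under Stage 4: "Stage 4 can last from one to three months".

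**When stage 4 is given.** Under Stage 3: "When stage 3 has not been effective in ensuring the recovery among professionals, a fourth stage can be added". Under Stage 4: "This optional stage is notably delivered if several suicides occurred or if the whole team is highly impacted by the suicide(s").

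**Analysis.** Under Quantitative analysis, total scores are compared between T0 and T1 with a paired test and proportions beyond a cut-off with McNemar's test. The IES-R score, named there as the main outcome criterion, also gets a linear mixed model adjusted for age, gender, profession and relationship with the deceased. Time since the suicide, the T0-T1 interval and receipt of stage 4 are not among the listed adjustments. Expected Results acknowledges that the study is uncontrolled.

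**The concern.** An end-of-program measurement is harmless when the program has one length. Here the length may vary, and one reason for extending it is that the team has not recovered. Read literally, follow-up time then depends on the outcome being measured.

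In an uncontrolled before-after study the change score contains whatever recovery would have occurred anyway. If symptoms decline with time, a team that gets more weeks before T1 shows a larger fall without any greater program effect. If the extra weeks go mainly to slowly recovering teams, their state at the end of the mandatory stages is never recorded and their slower course is understated. Nothing in the stated analysis would reveal or correct this, and all four quantitative outcomes share the same T1.

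**Working it through.** **1. Can the stated length contain stage 4?** Three mandatory stages come first, then stage 4 of one to three months. One month is 30.4 / 7 = 4.3 weeks and three months is 91.3 / 7 = 13.0 weeks. Even the short version would leave 6 - 4.3 = 1.7 weeks for stages 1 to 3, although the Stage 2 text allows the team intervention to take place at any point in the month after the suicide. The long version exceeds six weeks by itself. The six-week, four-stage description and the stage 4 duration cannot both describe the same span.

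**2. Two readings of T1.** Assume that the six weeks cover the mandatory stages and that stage 4 starts when they end.

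| Reading | Team without stage 4 | Team with stage 4 |
|---|---|---|
| T1 after the mandatory stages | about week 6 | about week 6 |
| T1 after the last stage given | about week 6 | 6 + 4.3 = 10.3 to 6 + 13.0 = 19.0 weeks |

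On the second reading, T1 comes 10.3 / 6 = 1.7 to 19.0 / 6 = 3.2 times later in stage 4 teams.

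**3. Is the delay related to outcome?** Partly. Lack of recovery after stage 3 and high impact on the whole team are both reasons for stage 4. Several suicides are another, and the stage is optional throughout.

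**4. Direction, by illustration only.** The documents give no recovery curve, so every half-life here is an assumption. Let scores fall exponentially with time alone, with no program effect: fall = 1 - 0.5^(weeks / half-life). Take five equal teams with equal baselines, two of them slow and given stage 4.

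- Half-life 12 weeks (ordinary) and 26 weeks (slow). Ordinary teams at week 6: 29.3%. Slow teams: 14.8% at week 6, 24.1% at 10.3 and 39.8% at 19.0.
  - Pooled, all at week 6: (3 × 29.3 + 2 × 14.8) / 5 = 23.5%.
  - Pooled, T1 after stage 4: (3 × 29.3 + 2 × 24.1) / 5 = 27.2% up to (3 × 29.3 + 2 × 39.8) / 5 = 33.5%.
- Half-life 8 and 16 weeks, same layout: 33.5% with a common T1, 38.8% to 46.8% with T1 after stage 4.

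Under the first pair of assumptions, slow teams at week 19 would appear to have improved more (39.8%) than ordinary teams at week 6 (29.3%). The inflation of the pooled fall ranges from 27.2 - 23.5 = 3.7 to 46.8 - 33.5 = 13.3 percentage points across these cases, and it is zero if T1 is common. These figures show direction and sensitivity; they do not estimate the bias in this study.

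**5. Could the model repair it afterwards?** Not reliably. There are only five implementations and stage 4 is given to teams, so a stage 4 delay would be largely a between-team difference, entangled with the severity that led to stage 4. An elapsed-time term can handle scatter around a common T1, but it cannot replace one.

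**The case against.** The strongest reply is that no sentence says T1 waits for stage 4. Six weeks may well mean the mandatory stages, with T1 at about week 6 for all. Figure 3, on participants' trajectories, is not in the text reviewed and may settle this, and an article can leave visit windows to the full protocol. The schedule also leans that way: the article plans its work as "including a total of five SUPPORT interventions over a total of 15 months", or 15 / 5 = 3 months (about 13 weeks) per cycle on average, with analysis, workshop and adaptation to be completed before the next implementation. A week 19 T1 would not fit an average cycle, though one cycle could run longer. **This stands**, and it makes the bias conditional. It does not remove the conflict over what the program spans, on which the meaning of T1 depends.

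Three stronger readings are tempting and should be resisted.

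- *Non-recovery would be hidden.* A reader might infer this, but a team still unwell at a late T1 would still score high on totals and cut-offs. What is lost is its state at a common time, so slow recovery would be understated.
- *Stage 4 teams are simply the worst teams.* Repeated suicides also lead to stage 4, and a further suicide could raise T1 scores. The direction is therefore a tendency. Nor can a steady 30% fall per six weeks be projected to weeks 10 and 19 to size the bias: it uses the planned effect as the natural course and applies it to teams selected partly for not recovering.
- *T0 should be moved ahead of stage 1.* Stage 1 acts "during the first days following a PUS", and the IES-R covers the previous seven days. An earlier T0 would reach further back before the event. No such change is supported.

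It is also fair that effectiveness is a secondary objective, that the article disclaims definitive inference, and that the program is deliberately modified between implementations. This lowers the severity, but does not justify an undefined endpoint time for the outcome on which the sample size rests.

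**Conclusion.** The concern holds in conditional form and is of moderate severity. Two things are established from the text: the statements on program length conflict, and T1 inherits the conflict because it is defined only by the program's end. If T1 follows stage 4, teams selected partly for slow recovery are measured at about 10 to 19 weeks instead of about 6, and the pooled T0-T1 change is biased toward improvement provided that scores decline with time. If T1 is common at about week 6, no such bias arises. The timing range assumes that stage 4 begins at week 6; the size of any bias cannot be derived from the documents.

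**What to change.** 1. Reconcile the six-week, four-stage description with the one-to-three-month stage 4, and say what the end of the program means for measurement.
2. Set T1 at one interval with a window for every participant, for example about week 6, the stated program length, whether or not stage 4 is given. Questionnaires should follow the calendar and must not delay any support.
3. Where a measure after stage 4 is wanted, add it as T2 and report it descriptively, outside the T0-T1 comparison.
4. Record days from the suicide to T0 and to T1, and include elapsed time in the IES-R mixed model to absorb variation within the window.

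The cost is protocol wording, two recorded intervals per participant and, if T2 is kept, one extra self-report questionnaire for stage 4 teams. Items 2 and 3 need to be settled before data collection, because a missed common T1 cannot be recovered in the analysis.
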